### Other Endpoints

Neurobehavioral outcomes after cardiac surgery (180 days)Quality of life after cardiac surgery (180 days)Cost (180 days)

### Statistical Analysis

The sample size of the FRAGILE trial was based on the ability to detect a 40%
reduction in the primary outcome in the off-pump group compared with the on-pump
group, assuming an event proportion after on-pump CABG of 20.8% and accepting a
risk of type I and II error of 5% and 20%, respectively, and a crossover rate of
5%^[24]^. Consequently,
at least 630 patients will be enrolled.

All of the data will be analyzed according to intention-to-treat
(*i.e.*, based on treatment allocation). Therefore, we will
report treatment-received analyses according to the intervention actually
received. Baseline characteristics and operative characteristics will be
compared with the use of chi-square test, t-test, or Kruskal-Wallis test, as
appropriate. Dichotomous data will be presented as numbers and percentages.
Continuous data will be presented as mean and standard deviation or median and
interquartile range. The continuity corrected chi-square test will be used for
comparison of the 30-day endpoint. Mantel-Haenszel chi-square tests will be used
to adjust for study-center effects. Treatment effects at 30 days will be
expressed as OR and 95% CI. For the 12-month endpoint, Kaplan-Meier curves will
be constructed, and the study groups will be compared with use of the log-rank
test. HR and 95% CI derived from the Cox proportional hazards model will be
provided for the composite outcome and individual components. All statistical
analyses will be performed with the use of the R-3.1.2 language for handling and
storage of data and performing of statistical calculations.

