**Methods:**

FRAGILE is a two-arm, parallel-group, multicentre, individually randomized
(1:1) controlled trial which will enroll 630 patients with blinded outcome
assessment (at 30 days, 6 months, 1 year, 2 years and 3 years), which aims
to compare adverse cardiac and cerebrovascular events after off-pump
*versus* on-pump CABG in pre-frail and frail patients.
Primary outcomes will be all-cause mortality, acute myocardial infarction,
cardiac arrest with successful resuscitation, low cardiac output
syndrome/cardiogenic shock, stroke, and coronary reintervention. Secondary
outcomes will be major adverse cardiac and cerebrovascular events, operative
time, mechanical ventilation time, hyperdynamic shock, new onset of atrial
fibrillation, renal replacement therapy, reoperation for bleeding,
pneumonia, length of stay in intensive care unit, length of stay in
hospital, number of units of blood transfused, graft patency, rate of
complete revascularization, neurobehavioral outcomes after cardiac surgery,
quality of life after cardiac surgery and costs.

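### The 630 patients are the requirement with no crossover; with the stated 5% crossover, power is about 72% to 77%, or 68% to 73% with the planned continuity-corrected test, not 80%

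*Protocol article*

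**What the plan says.** The sample-size paragraph (Methods, Statistical Analysis) targets a relative reduction of 40% in primary-outcome events, from an on-pump rate of 20.8%. The error rates and the crossover assumption appear together ("risk of type I and II error of 5% and 20%, respectively, and a crossover rate of"), the crossover figure being 5%. The paragraph presents the total as the result of these inputs: "at least 630 patients will be enrolled". Allocation is 1:1 (Abstract, Methods), so there are 315 patients per arm.

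The same section makes intention-to-treat the main analysis, with a treatment-received analysis reported as well. For the 30-day endpoint the planned test is the corrected one ("The continuity corrected chi-square test will be used for"), and effects are given as odds ratios with 95% confidence intervals. It does not state whether the 5% error is one- or two-sided, which way the 5% crossover runs, or which sample-size formula was used.

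**The concern.** Crossover is listed as one of the inputs that lead to 630. In an intention-to-treat comparison, crossover moves the two arms' event rates towards each other, so a real allowance must raise the sample size above the no-crossover figure. Yet 630 is almost exactly the no-crossover figure. In addition, the test named for the 30-day endpoint is more conservative than the test behind that figure.

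What is at stake is how the result is read. The article says the trial will determine whether off-pump surgery is superior. If readers believe the trial had 80% power for a 40% reduction, they will take a non-significant result as stronger evidence against that reduction than it is.

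**Working it through.** **Inputs**, all from Statistical Analysis except the allocation ratio (Abstract):
- on-pump rate p1 = 0.208
- off-pump rate p2 = 0.6 × 0.208 = 0.1248, a difference of 0.0832
- type I error 5%, taken as two-sided (z = 1.960); power 80% (z = 0.842)
- 1:1 allocation, 315 per arm
- 5% crossover, direction not given

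**1. Reproducing 630.** The pooled two-proportion formula per arm is

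n = [1.960·√(2p̄(1−p̄)) + 0.842·√(p1(1−p1) + p2(1−p2))]² / (p1−p2)², with p̄ = 0.1664.

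The two terms in the bracket are 1.0323 and 0.4405. Their sum squared, divided by 0.0832² = 0.006922, gives n = 313.4, so 314 per arm and **628** in total. Using the pooled variance in both terms gives 314.6, so 315 per arm and **630** exactly. The unpooled formula gives 622. The stated number is therefore reproduced with no crossover allowance.

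**2. Adding the 5% crossover.** Patients who cross are given the risk of the treatment they receive, and the arms are compared as randomised.
- Off-pump to on-pump: the off-pump arm becomes 0.95 × 0.1248 + 0.05 × 0.208 = 0.12896
- On-pump to off-pump: the on-pump arm becomes 0.95 × 0.208 + 0.05 × 0.1248 = 0.20384
- Both: 0.20384 versus 0.12896

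Total N for 80% power, from the formula above and from its continuity-corrected version n/4 × [1 + √(1 + 4/(n·|p1−p2|))]²:

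| Crossover | Difference | N, uncorrected | N, continuity-corrected |
|---|---|---|---|
| None | 0.0832 | 628 | 674 |
| On-pump to off-pump | 0.0790 | 688 | 738 |
| Off-pump to on-pump | 0.0790 | 702 | 752 |
| Both arms | 0.0749 | 776 | 828 |

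For the uncorrected test, 630 is 58 to 146 patients short. Simple inflation of 628 does not return 630 either: ×1.05 gives 660, /0.95 gives 662 and /0.95² gives 696.

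**3. What 315 per arm delivers.** Power was found by enumerating both binomial distributions and applying the two-sided 5% chi-square test to every possible outcome. The last two columns give the relative reduction detectable with 80% power, found the same way.

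| Crossover | Power, uncorrected | Power, corrected | Detectable reduction, uncorrected | Detectable reduction, corrected |
|---|---|---|---|---|
| None | 80.6% | 77.4% | 39.7% | 41.1% |
| On-pump to off-pump | 76.9% | 73.3% | 41.4% | 42.9% |
| Off-pump to on-pump | 76.0% | 72.4% | 41.8% | 43.3% |
| Both arms | 71.8% | 67.9% | 43.7% | 45.2% |

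The normal approximation agrees to within half a percentage point (80.2%, 76.5%, 75.6% and 71.4% uncorrected).

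**The case against.** **The test could be one-sided.** Sidedness is not stated. At one-sided 5%, the pooled formula needs 542 or 554 with one-way crossover and 610 with crossover in both arms, so 630 would suffice for the uncorrected test. But none of these is 630. A few one-sided calculations on other scales, inflated by 1/0.90², do land near it (624 to 635), but they require several choices the article never states. Two-sided chi-square tests and 95% confidence intervals point the other way.

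**A time-to-event formula could have been used.** A Schoenfeld calculation (607) inflated once by 5% gives 638 or 639. However, the 30-day endpoint is analysed as a proportion, and a single 5% inflation understates intention-to-treat dilution.

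**The 40% could already be net of crossover.** Then 630 would be adequate for the uncorrected test. The paragraph lists crossover as a separate input, which does not fit that reading. Even so, the planned corrected test would have only about 77% power.

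**Two effects are combined, and the loss is modest.** This is partly fair. The continuity correction is a separate matter from crossover, which is why the tables keep them apart. Crossover alone takes the type II error to 23% to 28%; only crossover in both arms plus the correction gives 32%. With one-way crossover and no correction, the loss is about 4 points. The 630 is also a minimum, and the reported confidence interval will itself show which reductions are excluded. Type I error is not affected. None of this makes the stated power correct.

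**Centre-adjusted Mantel-Haenszel tests are also planned.** Their power was not calculated here. Adjusting for centre does not undo the shrinkage of the difference that crossover causes.

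**Conclusion.** The concern holds. Under a two-sided 5% test, 630 is the sample size with no crossover, so the article claims 80% power under an assumption its number does not include. With 5% crossover, power is 72% to 77% for the uncorrected test and 68% to 73% for the continuity-corrected test that the section names. The type II error is 23% to 32% rather than 20%.

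The result rests on three assumptions: a two-sided test, the 40% reduction being the effect before crossover, and crossed patients carrying the risk of the treatment received. The width of the range comes from the unstated direction of crossover and the choice of test. Crossover cannot be waved away as negligible: the Introduction cites conversion rates of 12.4%, 7.9% and 5% in three earlier trials, so 5% is the lowest of the three, although it also cites 2% to 4% for expert centres.

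**What to change.** Correct the sample-size statement. State that the test is two-sided and which way the 5% crossover is assumed to run, then give the figure for the test that will be used. For the uncorrected chi-square test, the text could read:

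> With 630 patients and a two-sided 5% test, power for a 40% reduction from 20.8% is 80% with no crossover, 76% with 5% crossover from off-pump to on-pump, and 72% with 5% crossover in both arms.

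Equivalently, give the reductions detectable with 80% power: about 42% and 44%. If the continuity-corrected test is kept, the figures become 77%, 72% and 68%, and the detectable reductions under the two crossover cases about 43% and 45%. Dropping the correction would bring the test into line with the formula behind 630.

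The cost is one sentence and a slightly less favourable power statement. No extra patients are required. If the sponsor would rather keep 80% power with 5% crossover, the price is a total of 688 to 776 patients uncorrected, or 738 to 828 corrected, depending on direction.

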### Study Population

The inclusion criteria will be: participants aged ≥65 years with
indication of myocardial revascularization with ≥2 criteria of frailty by
Fried Frailty Criteria^[16]^,
not eligible for angioplasty treatment by the heart team approach and those
suitable to undergo either off-pump or on-pump CABG.

There is a dose-response relationship, in relation to the number of fragility
criteria and patient outcomes. The categorization of the fragility variable was
performed after the studies showed that the risk increases gradually over 3
categories (0-1, 2-3, 4-5), with risk of similar events within each category.
Thus, patients who had 2 or 3 criteria were considered as pre-frail, and
patients with 4 or 5 criteria were considered as frail^[21]^.

The exclusion criteria will be: patients with indication of another procedure in
addition to CABG; patients who underwent emergency operation (within 24 hours
after hospital admission); patients who underwent previous cardiac surgery, even
with other approaches than median sternotomy; patients who do not have free,
prior and informed consent to participate in this study.

The baseline characteristics of potentially eligible but excluded patients will
be recorded in a screening log. All patients will be provided written informed
consent.

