### Randomization and Treatment

Eligible patients will be randomly assigned to off-pump CABG or on-pump CABG.
Randomization will be performed after the baseline data, including information
about the target vessels have been entered into a central, Internet-based,
password-protected database with the use of a template.

Treatment assignments will be performed in a blinded manner according to a
blocked randomization scheme with a block size of ten, stratified according to
the participating center. Off-pump CABG must be routinely performed at all
participating centers before the trial is initiated. Participating centers
should nominate individual study surgeons for each surgical technique.

Study surgeons will be required to be established experts in the performance of
either off-pump or on-pump CABG. The average number of CABG surgeries performed
before the study will be between 50-100 off-pump surgeries for the off-pump CABG
surgeons and 250 on-pump surgeries for the on-pump CABG surgeons. It will not be
mandatory for the same surgeon who operates the off-pump CABG cases to also
operate the on-pump CABG cases, but always respecting the established protocols
for each surgical technique.

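### The 30-day primary endpoint is to be tested with a continuity-corrected chi-square, but 630 patients were sized for an uncorrected test; the named test has about 77% power, not 80%

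*Protocol article*

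**What the plan says.** The Primary Endpoint section sets the endpoint at 30 days after surgery. The Statistical Analysis section assigns the test: "The continuity corrected chi-square test will be used for" and, running on, "comparison of the 30-day endpoint. Mantel-Haenszel chi-square tests will be used". The second of these sentences gives the purpose of the Mantel-Haenszel tests as adjustment for study-centre effects. The section then says that 30-day effects will be reported as odds ratios with 95% confidence intervals, without saying which analysis supplies them.

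The sample size in the same section is "based on the ability to detect a 40"% reduction, "assuming an event proportion after on-pump CABG of 20.8"%, with a "risk of type I and II error of 5% and 20%, respectively", "and a crossover rate of" 5%. The result is at least 630 patients.

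Under Randomization and Treatment, allocation follows a "blocked randomization scheme with a block size of ten, stratified according to" the participating centre. The Study Design section gives ten institutions.

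**The concern.** A continuity correction protects the type I error when a table is sparse. This table will not be sparse, so the correction only makes the test conservative: it spends less than the 5% type I error on which the sample size was built, and power falls below the stated 80%. If the sample size calculation left the correction out, the trial is sized for one test and committed to another. Because the protocol names the corrected test outright, a fuller analysis plan could not cure this without contradicting it.

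The named test also leaves out the one factor by which the trial randomises. The centre-adjusted test is in the plan, but the comparison of the endpoint is assigned to the unstratified one.

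**Working it through.** **Inputs.** From Statistical Analysis: on-pump proportion p1 = 0.208; 40% relative reduction, so p2 = 0.6 × 0.208 = 0.1248; type I error 5%; power 80%; N = 630, or 315 per arm at 1:1. From these, d = 0.0832 and mean proportion 0.1664. Sidedness is not stated; two-sided is assumed.

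**1. Reproduce 630.** Pooled-variance formula, no correction:

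n = [1.960·√(2 × 0.1664 × 0.8336) + 0.8416·√(0.208 × 0.792 + 0.1248 × 0.8752)]² / 0.0832²
= (1.0323 + 0.4405)² / 0.006922 = 313.4, so 314 per arm and **N = 628**.

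This matches 630. It contains no continuity correction and no crossover allowance.

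**2. The same with the correction.**

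n_c = (n/4)·[1 + √(1 + 4/(n·d))]², with n·d = 313.4 × 0.0832 = 26.07
= 78.34 × (1 + 1.0740)² = 337.0 per arm, so **N = 674**.

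The difference is 674 − 628 = 46 patients. A one-sided test gives 494 uncorrected and 542 corrected. None of the crossover allowances tried brought a corrected formula, one- or two-sided, to within 3% of 630.

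**3. Is a correction needed?** Expected events are 315 × (0.208 + 0.1248) = 104.8, about 52 per arm under the null. With equal arms and x, y events (total t), the uncorrected statistic is 630(x − y)²/[t(630 − t)]. The correction replaces |x − y| by |x − y| − 1. For example, 65 against 46 events gives 630 × 19²/(111 × 519) = 3.95 (p = 0.047) uncorrected, and 630 × 18²/(111 × 519) = 3.54 (p = 0.060) corrected.

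**4. Exact power and size at 315 per arm.** Binomial probabilities are summed over all pairs (x, y) whose statistic exceeds 3.84. Crossover moves a proportion by 0.05 × 0.0832 = 0.00416.

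| Scenario | Uncorrected | Corrected | Loss (points) |
|---|---|---|---|
| 20.8% vs 12.48% | 80.6% | 77.4% | 3.2 |
| 5% crossover off-pump to on-pump (20.8% vs 12.90%) | 76.0% | 72.4% | 3.5 |
| 5% crossover both ways (20.38% vs 12.90%) | 71.8% | 67.9% | 3.9 |

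Losses are taken before rounding. Under the null at 12.48%, 16.64% and 20.8%, the corrected test rejects in 3.73%, 3.86% and 3.98% of trials. The uncorrected test rejects in 4.96% to 5.02%.

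**5. What stratifying by centre adds.** Simulation of 20,000 trials per scenario with ten centres. The between-centre SD on the logit scale is assumed, since the protocol gives none.

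| Centre SD | Corrected chi-square | Uncorrected chi-square | Mantel-Haenszel, uncorrected | Mantel-Haenszel, corrected |
|---|---|---|---|---|
| 0 | 77.5% | 80.7% | 80.6% | 77.5% |
| 0.3 | 77.7% | 81.0% | 81.2% | 78.0% |
| 0.5 | 77.6% | 80.9% | 81.6% | 78.4% |

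A separate run at SD 0.6 gave 77.6%, 80.7% and 81.8% for the first three tests. Centre therefore adds about 0 to 1 point beyond removing the correction. A Mantel-Haenszel test that keeps the correction also recovers only 0 to about 1 point over the named test. Under the null, the uncorrected Mantel-Haenszel test rejected in 5.0% to 5.2% of trials.

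**The case against.** The strongest defence is that a continuity-corrected test is a recognised, pre-stated and conservative choice, which cannot by itself produce a falsely positive trial. That stands: the issue is lost power and a mismatch with the sample size, not validity. The mismatch remains, because 630 does not give this test its stated power.

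Three stronger readings are tempting, and the protocol does not support them.

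- *The analysis ignores centre.* It does not: the sentence after the named test plans a Mantel-Haenszel adjustment for centre. What can be said is that the adjusted test is not the one assigned to the comparison.
- *There are two competing primary p-values.* The natural reading is a main test with a supporting adjusted analysis, and a formal ranking is commonly left to the analysis plan. Little could be gained by choosing between them: claiming success on either rejected at most about 5.2% under the null in simulation. The two tests fell on opposite sides of 0.05 in about 3% to 5% of trials under the planned effect, which is ambiguity and not material inflation.
- *Frailty category should be in the test because the Study Population section says* "There is a dose-response relationship, in relation to the number of fragility" *criteria.* Frailty is not a randomisation factor, and covariate choice normally belongs in the analysis plan. Even with an assumed odds ratio of 2.5, 25% frail and centre SD 0.6, adding frailty strata to centre moved power only from 81.2% to 81.5%, which is within simulation error. When frailty was not prognostic, the extra strata cost about half a point.

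It is also fair that most of the fall to 67.9% in the worst scenario comes from crossover dilution. That is a separate sample-size matter; only the 3.9-point difference belongs here.

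**Conclusion.** The point holds, at modest size. The named test has 77.4% power at 630 patients under the protocol's own proportions, where 80% is stated. It uses 3.7% to 4.0% of the 5% type I error. Against the uncorrected test the loss is 3.2 points, rising to 3.9 with 5% crossover in both directions. Nearly all of it comes from the continuity correction. The missing stratification accounts for about 0 to 1 further point.

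The power and size figures rest on a two-sided 5% test, 315 analysed per arm, and 20.8% against 12.48% before crossover. The centre figure also rests on an assumed logit SD of 0 to 0.6.

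**What to change.** In Statistical Analysis, make the Mantel-Haenszel test stratified by centre, **without continuity correction**, the single primary test of the 30-day endpoint, and report its common odds ratio with 95% confidence interval. State the absence of the correction explicitly: the planned software, R, applies it by default, so `correct=FALSE` must be set. Label the unstratified corrected chi-square a sensitivity analysis.

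This costs a wording change, with no new data and no additional patients. It restores the planned 5% size and about 80% power before crossover.

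If the corrected chi-square is kept as the deciding test, restate its power at 630 as about 77% before crossover, or enrol the 674 that it needs for 80%.

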## DISCUSSION

The elderly represent the fastest growing group of patients referred for cardiac
surgery, with the proportion of patients aged 75 years or older steadily rising from
16% in 1990 to 25% in most recent estimates^[25]^. Advanced age is frequently accompanied by a larger burden
of comorbid conditions and greater illness severity. In the setting of cardiac
surgery, elderly patients are more likely to have extensive coronary artery disease
and concomitant valvular disease and are more likely to require urgent or emergent
surgery^[26]^.

Nevertheless, elderly patients have consistently been shown to derive sizeable
benefits from cardiac surgery^[27]^.
This risk-benefit dichotomy renders the process of selecting appropriate elderly
patients particularly challenging for the cardiac surgeon.

Frailty is defined as a geriatric syndrome of impaired resiliency to stressors that
has been delineated recently in the cardiovascular literature^[28]^. In several observational studies
and registry data in which detailed statistical analyses were carried out, mortality
and morbidity have been found to be significantly reduced after off- pump CABG
compared with on-pump CABG in high-risk patients (*e.g.*, patients
with advanced age or cardiac and systemic comorbidity)^[8,12-14]^.

The results of BBS randomized trial are in contrast to these findings. Overall 30-day
mortality in this trial was 4.4%, which was less than the predicted mortality rate
of 7% according to the EuroSCORE but in agreement with the predicted 3.1% according
to the STS risk score. This study shows that the risk patients were overestimated by
the EuroSCORE and this sample will be composed of low and moderate risk patients by
the STS risk score^[9]^.

In the GOPCABE trial, there was no significant difference between off-pump CABG and
on-pump CABG performed in elderly patients with respect to the composite endpoint of
death, stroke, myocardial infarction, repeat revascularization, or new renal
replacement therapy after surgery. With a mean age of 78 years and a predicted
in-hospital mortality of 3.8%, the study cohort does not represent a population with
a high operative risk. The results of previous studies are consistent with regard to
high-risk patients^[16-18]^.Therefore, this trial does not
support the assumption that off-pump CABG cannot improve the early outcome in
high-risk patients.

In contrast to the ROOBY trial^[11]^,
the GOPCABE study did not show a significant difference in survival or major adverse
events at 1 year after surgery. This absence of difference may be a consequence of
the requirement for substantially greater experience with off-pump CABG in the
GOPCABE trial than in the ROOBY trial.

With the growth of minimally invasive and transcatheter cardiac interventions, the
expansion of risk prediction beyond traditional risk factors and risk scores has
become a high priority. Clinicians may use this integrative approach of combining
risk scores including frailty and disability to better characterize elderly patients
referred for cardiac interventions and identify those who are vulnerable and at
increased risk. A multidisciplinary team involving cardiac surgery, cardiology,
geriatric medicine, physiotherapy, and occupational therapy may be well suited to
address these diverse elements which contribute to postoperative risk^[19]^.

The CORONARY trial falls short of delivering a knockout victory for the off-pump
technique. There were no significant differences in the rate of the composite
primary outcome of death, stroke, non-fatal myocardial infarction or new renal
failure at 30 days between off-pump and on-pump CABG. However, off-pump CABG was
associated with fewer transfusions, reoperations for bleeding, acute kidney injury,
and respiratory infections or failure. Thus, the off-pump technique may be best in
certain subgroups of patients and we must choose the procedure that is best for
them^[29]^. We hypothesized
that the frailty status would contribute to the risk in patients undergoing on-pump
CABG and that off-pump CABG could be advantageous for frail patients.

